**Figure 1 F1:**
[figure not shown]
**Flowchart of the RCT with intervention and control groups**.

The bar graph format to be used in the two control groups consists of vertical bar graph depicting percentages. This will be animated (growing upwards) to demonstrate the wide confidence intervals of the risk categories in the Personal Risk Score [47]. A bar graph has been chosen as it is the standard presentation format commonly used in current risk prediction tools. A pictogram of 100 hearts depicting natural frequencies will be used in intervention group 1. Research shows that these formats are better understood by patients, natural frequencies intuitively offer more insight than other formats [9,10] and pictograms help the viewer see the risk in context and facilitate accurate judgements of probability [48,49]. Again, this format will be animated, highlighting each affected heart in turn, to account for the range of numbers affected in the risk category. A metonym format will be used in intervention group 2. This will depict the seriousness of an emergency admission for a myocardial infarction. This has been chosen as heart disease is generally associated with having a myocardial infarction [50]. An image demonstrating healthy longevity will be shown to those in the low risk category; those at moderate risk will be shown an ambulance traveling towards a person's house, and a person being defibrillated will be shown to the high risk category.

To assess changes in emotional affect and worry, all respondents will have these measured at baseline during the risk assessment. Those in the bar graph and pre-intervention questionnaire group (control group 1) will also complete a partially parallel version of the post-intervention questionnaire. This is to address the Hawthorne effect of the four groups, and compare those who are asked to think about their cardiovascular risk and their prior intentions to reduce this, against those who are not. However, to keep the total number of items to a minimum, the focus is on reducing overall cardiovascular risk, instead of specific behaviours that lead to risk reduction. All respondents will view the risk in the format that they have been randomly assigned to and complete the post-intervention questionnaire.

There will be two main comparisons:

1. (a) Bar graph only v. Pictogram

(b) Bar graph only v. Metonym.

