### vi) Outcome Assessment

Outcomes will be assessed by means of a self-complete on-line questionnaire integrated into the web-based formatter. Reliability measures, such as Cronbach's alpha for internal reliability, will be carried out on the questionnaire items at the piloting stage of this trial. Items not meeting the reliability requirements will be eliminated from the final questionnaire. To address possible response bias occurring from fatigue, items measuring the different outcomes and components of the TPB will be mixed up in the questionnaire (as recommended by Ajzen [51]).

The primary outcome measures are:

(i) *Intention to change behaviour- *Items relating to cardiovascular risk reduction were developed using guidance from a manual for constructing questionnaires based on the TPB [52]. This manual was chosen as it has been widely used in previous research that has required TPB questionnaire development [53-55]. It also provides a way of measuring the TPB contrasts directly, reducing the number of items and thus, keeping the cognitive demand of respondents to a minimum. The questionnaire items comprise three risk reducing options of: smoking cessation, exercising more and losing weight. These are the three modifiable risk factors assessed by the Personal Heart Score. The relevance of these risk reducing options will be assessed. Questions relating to smoking will only be asked to those who reported that they are current smokers; adjustment will be made for this during analysis. Responses for intention to lose weight will be assessed for appropriateness (e.g. whether those who do not report this intention actually need to lose weight). Scale items such as *'I intend to exercise more' *with a 7-point Likert response options will be used. An indirect measure of intention to change behaviour will be also assessed, by examining whether individuals take the opportunity to obtain a copy of their risk output to take to their GP.

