*(ii) Understanding *- Items specific to the understanding of cardiovascular risk information have been developed and will be piloted, as no suitable validated scale currently exists. These comprise absolute probability perception e.g. *'What are your chances of having heart disease in the next 10 years?' *with three pre-defined response options (low, moderate, high*)*; subjective understanding of the risk information e.g. '*What should someone in your risk category do to reduce their risk of heart disease*?' with 3 pre-defined response options (do nothing to reduce their risk, try and do a little bit to reduce their risk, do as much as they can to reduce their risk); and confidence in understanding e.g. '*How confident are you that you have understood the risk information given to you?' *with a 7 point Likert Scale to indicate level of confidence in understanding.

*(iii) Emotional affect after viewing cardiovascular risk - *The Positive and Negative Affect Schedule- Short Form (PANAS-SF) will be used [56]. This is a 10-item truncated version of the PANAS, which has been well validated and cited in over 2,000 scholarly papers [57]. It was felt that the original 20-items would be too time-consuming and cognitively demanding for respondents, possibly leading to high drop out rates. As this study is interested in respondents' changes of affect after viewing their risk output, a slight adaptation to the wording of the instructions and anchors/pole labels was made to the post-intervention scale, to make it more logical. An example of one item is: '*Thinking about yourself right now at this present moment, to what extent do you feel upset?' *with a 5-point Likert response scale anchored *'not at all' *to *'extremely'*.

*(iv) Worry about future heart disease - *one item will be used to measure this construct, in order to keep the total time needed to complete the questionnaires to a minimum. No previously developed and validated scale regarding worry about future risk of heart disease currently exists. Therefore, the item was developed using previously validated scales relating to other health conditions, such the Lerman Breast Cancer Worry Scale [58] as a guide. This item is '*After viewing your results, how worried do you feel about developing heart disease in the future?*' with '*very worried' *to '*not at all worried' *anchored on a 7-point Likert response scale.

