### viii) Analysis

The results will stored on a SQL database and fed back to the researcher via the server that hosts the website. The data will be stored on the shared drive which will be password protected and only accessible to the researcher. Data will be retrieved, coded and inputted into computer software. Microsoft Office Excel 2007 will be used for data manipulation and SPSS version 16 for the main data analyses.

The usual descriptive statistics will be presented to summarise baseline characteristics of the study sample. Continuous variables such as age and level of cardiovascular risk will be summarised using mean and SD and/or median and quartiles. Binary variables such as gender and whether the respondent requests an electronic copy of their risk output for their GP will be summarised by counts and proportions. Summary statistics will be obtained for the study population as a whole, and for the four randomised groups, without formal testing of statistical significance of any differences between them.

The main analyses of efficacy will relate to the primary outcome measures: intention to change behaviour, understanding of risk information, emotional affect and worry about future heart disease. Summary statistics for the four groups will be presented, as above. The four groups will first be compared on an equal footing using one-way ANOVA. The three selected pairwise contrasts between the specified groups, will then be constructed (e.g. bar graph only v. pictogram; bar graph only v. metonym; and bar graph and preintervention questionnaire v. bar graph only).

Several secondary analyses will be performed. For the bar graph and preintervention questionnaire group (control group 1), paired analyses will be used to assess serial changes in outcome measures between pre- and postintervention questionnaires.

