A multiple regression model will be used in a sub-group analysis to look for correlations between risk category on intention to change behaviour, understanding of risk and post worry about future heart disease outcomes, to see if responses are mediated by risk category. It will also be used to assess the correlational validity between intention to change behaviour, worry about future heart disease and understanding of risk information; to determine what level of worry increases intention to change behaviour and whether understanding also results in appropriate intentions. The subcomponents of the TPB (attitudes, perceived behavioural control and subjective norms) will also be examined, to see if they sufficiently predict intention to change behaviour (in order to test the efficacy of the model in predicting cardiovascular-related behaviour change).

The direct and indirect measures of intention to change behaviour will be correlated, to see whether those who report that they intend to change their behaviour actually take the opportunity to print out their risk output to take to their GP. Furthermore, a correlation between accurate understanding of risk information and confidence in understanding will be conducted. Lastly, Independent T-tests will compare baseline and post-intervention emotional affect and worry about future heart disease scores, to determine whether scores generally decrease after viewing a particular risk presentation format, or increase, demonstrating a possible negative impact.

For all analyses, point and interval estimates will be obtained, as well as p-values. In the event of substantial departure from Gaussian distributional form, transformation of scale and/or analogous non-parametric methods will be considered.

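### The affect scale is reworded between baseline and post-intervention, so within-arm change in affect cannot be attributed to the risk format; the randomised between-arm comparisons are not affected

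*Protocol article*

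**What the plan says.** Three statements in the protocol article bear on this.

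- **Methods/Design, v) Intervention and comparisons**, on why there is a baseline measurement: "To assess changes in emotional affect and worry, all respondents will have these measured at baseline during the risk assessment".
- **vi) Outcome Assessment, item (iii)**, on the PANAS-SF. The reason given for adapting it is "As this study is interested in respondents' changes of affect after viewing their risk output", and the adaptation is that "a slight adaptation to the wording of the instructions and anchors/pole labels was made to the post-intervention scale".
- **viii) Analysis**, on how change is tested and read: "Independent T-tests will compare baseline and post-intervention emotional affect and worry about future heart disease scores", the purpose being "to determine whether scores generally decrease after viewing a particular risk presentation format, or increase, demonstrating a possible negative impact".

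Two other analyses in the same section help to fix the scope. For the main efficacy analysis, "The four groups will first be compared on an equal footing using one-way ANOVA", followed by three pairwise contrasts. For control group 1, "paired analyses will be used to assess serial changes in outcome measures between pre- and postintervention questionnaires".

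The article nowhere mentions equating the two versions of the affect scale, testing their equivalence, or allowing for the rewording in the analysis.

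**The concern.** A baseline-to-post difference measures change only if the same instrument is used on both occasions. Here the instructions and pole labels change at the same moment as the exposure. A respondent whose feelings have not moved may still choose a different point on a relabelled 5-point scale. The planned reading assigns the whole difference to the display.

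Every arm is shown a risk format, so no arm would reveal a wording shift on its own. A shift common to all arms would look as if each format, including the standard bar graph, raised or lowered affect. At stake is the statement about a possible negative emotional impact of each format. If affect is among the measures repeated in control group 1's questionnaires, the paired analysis there is exposed in the same way.

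**Working it through.** **1. Structure.** Write the mean post-minus-baseline difference in arm *k* as *d_k + w*. Here *d_k* is the true effect of viewing format *k* and *w* is the effect of the rewording, taken as additive and common to all arms.

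- Within arm *k*, the analysis estimates *d_k + w*. Nothing in that arm's data separates the two terms.
- Between arms *j* and *k*, *w* cancels: (*d_j + w*) − (*d_k + w*) = *d_j − d_k*. The same holds for post scores alone and with baseline as a covariate.
- A paired test changes the standard error of *d_k + w*, not its expectation, so it does not remove *w*.

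**2. The plan's own figures.** The protocol gives no SD, correlation or target difference for affect. Its sample size calculation (200 per group, SD 1.5, difference 0.5, 90% power, α = 0.05) is for intention. It reproduces at about 91.5% power two-sided, but it does not bear on this point. Only the 200 per group is carried forward.

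**3. Illustration.** Assumptions from outside the documents: subscale mean on a 1 to 5 range, SD 0.8 on each occasion, pre/post correlation *r* of 0.4 or 0.6, no true change, normal approximation, two-sided 0.05.

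Actual SE of the mean change = 0.8 × √(2(1 − *r*)/200):
- *r* = 0.4: 0.062
- *r* = 0.6: 0.051

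SE used by an independent t-test, which ignores the pairing = 0.8 × √(2/200) = 0.080.

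Critical differences (1.96 × SE used):
- independent: 0.157
- paired: 0.121 (*r* = 0.4), 0.099 (*r* = 0.6)

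The probability of declaring significance in the direction of a shift *w* is 1 − Φ((critical difference − *w*)/actual SE). For *w* = 0.15:
- independent, *r* = 0.4: (0.1568 − 0.15)/0.0620 = 0.11, giving 46%
- independent, *r* = 0.6: (0.1568 − 0.15)/0.0506 = 0.13, giving 45%
- paired, *r* = 0.4: (0.1215 − 0.15)/0.0620 = −0.46, giving 68%
- paired, *r* = 0.6: (0.0992 − 0.15)/0.0506 = −1.00, giving 84%

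The same formula over a range of shifts:

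| Pure wording shift (points) | Independent t-test, r = 0.4 / 0.6 | Paired test, r = 0.4 / 0.6 |
|---|---|---|
| 0.05 | 4% / 2% | 12% / 17% |
| 0.15 | 46% / 45% | 68% / 84% |
| 0.20 | 76% / 80% | 90% / 98% |

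**4. Between-arm check.** In a simulation of two arms of 200 with correlation 0.5 and the same shift of 0.2 or 0.3 SD in both, the comparison of post scores rejected in 4.85% of 4,000 runs. The paired within-arm test on the same data rejected in about 81% and 99%. The randomised comparison keeps its error rate.

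**The case against.** The strongest reply is that the main analysis of affect is untouched. It is a one-way ANOVA with pairwise contrasts between randomised arms, and the protocol describes a single post-intervention scale that does not vary by arm. The objective of finding which format alters affect can be answered from those comparisons. The exposed analysis is the last of the listed secondary analyses, with possibly control group 1's paired analysis. This stands, and it limits the point. A reader might infer that the affect outcome as a whole is compromised; the documents do not support that.

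Second, the protocol describes the change as slight and prints neither wording in full, so the artefact may be negligible. This also stands. At a shift of 0.05 point the named independent t-test would rarely flag anything, because it overstates the standard error for paired data. But that protection comes from a test that does not suit repeated measures, and correcting the test removes it.

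Three further inferences go beyond the text.

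- That the mixing of items adds a second difference. The protocol says "items measuring the different outcomes and components of the TPB will be mixed up in the questionnaire", which can be read as covering the TPB items only, and the PANAS-SF has its own response format.
- That the cited validation does not extend to the altered version. The cited sources are not at hand; one can say only that the article cites no evidence of equivalence.
- That the printed example item is the adapted wording. The article does not say which version it shows.

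The absence of an analysis plan is not an answer. The protocol itself fixes different wording at the two times and states how the difference will be read.

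**Conclusion.** The point holds for within-arm change in affect. The instrument and the exposure change together, the plan attributes the difference to the exposure, and no analysis of the planned data can recover *w* within an arm. The randomised between-arm comparisons of post-intervention affect are not affected, provided the post scale is the same in every arm and any wording effect is common to the arms.

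The actual size and direction of a wording effect cannot be derived from the documents. The 45% (independent test) and 68% to 84% (paired test) for a 0.15-point shift rest on the assumed SD, correlations and shift. They show what a modest shift could do with 200 per arm, not what will happen in this trial. The point should be dealt with before the questionnaire is final; it does not threaten the main analysis.

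**What to change.** Use the same PANAS-SF instructions, anchors and items at baseline and post-intervention, whichever version is chosen.

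If the wording cannot be harmonised, delete from viii) Analysis the reading of within-format change in affect as impact. Base the affect conclusions on between-format differences in post-intervention score, with baseline affect as a covariate, and state that the two administrations differ in wording. The same restriction should then apply to any paired analysis of affect in control group 1.

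Replacing the independent t-test with a paired test is a separate correction and does not substitute for either step.

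Cost: a text edit to the web questionnaire, with no added items or respondents. The small downside is that one administration loses wording tailored to its timing. The fallback costs the within-format statement about affect.

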### vii) Sample size calculation

For simplicity, the sample size calculation is based on a comparison of means, though the analysis will recognise the ordinal nature of the data. It is hard to speculate on the difference between the groups and so the sample size is based on comparing 2 groups on the primary outcome measure which is intention to change behaviour; this will give a group size which will be used for all the groups. Recruitment will continue until 800 respondents (200 in each group) have completed the trial. The likely uptake rate is unknown and a number of the suggested recruitment methods may be needed. Based on a study that used a similar Likert Scale scoring system for a different risk context [59], the scores on intention to change behaviour within a group should have an SD of about 1.5. The total sample size in each group of 200 would then be sufficient to detect a difference of 0.5 point between two groups, with 90% power and significance value of *α = *0.05.

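### The sample size and its 90% power rest on one primary outcome and one two-group comparison, but four outcomes with three contrasts each are declared primary, and no hierarchy links them

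*Protocol article*

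**What the plan says.** Section vii) Sample size calculation treats the trial as having one primary outcome: "the sample size is based on comparing 2 groups on the primary outcome measure which is intention to change behaviour". It assumes that "the scores on intention to change behaviour within a group should have an SD of about 1.5", and concludes that 200 per group is "sufficient to detect a difference of 0.5 point between two groups" at a power of 90% and an alpha of 0.05. The target counts completers: "Recruitment will continue until 800 respondents (200 in each group) have completed the trial".

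Section viii) Analysis takes a different position: "The main analyses of efficacy will relate to the primary outcome measures: intention to change behaviour, understanding of risk information, emotional affect and worry". Section vi) Outcome Assessment lists the same four as primary, the abstract lists them as main outcomes, and Aims and Objectives gives each a primary objective. In section viii) the four groups are first compared by one-way ANOVA, and then "The three selected pairwise contrasts between the specified groups, will then be constructed": bar graph only v. pictogram, bar graph only v. metonym, and bar graph with v. without the pre-intervention questionnaire. The text does not say whether a significant ANOVA is a condition for reading the contrasts.

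The third contrast, which checks for a Hawthorne effect, also has two statuses. Aims and Objectives lists it as a secondary objective, while section v) Intervention and comparisons numbers it as one of the main comparisons.

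**The concern.** A reader cannot tell which result answers the trial's question. On the sample size section, the trial is decided by intention. On sections vi) and viii), any of four outcomes could support a conclusion, and each is compared through several contrasts. The Discussion says the findings will tell developers of risk tools which format works best, so the deciding result should be fixed before the data are seen.

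Two things are at stake. If all four outcomes count equally at 5%, the chance of at least one false format difference is well above 5%. And the 90% power was derived for intention alone: the document gives no standard deviation or target difference for understanding, affect or worry, which use partly different response scales.

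**Working it through.** **Inputs from section vii).** Difference 0.5, SD 1.5, 200 per group, alpha 0.05, power 90%. Sidedness is not stated; two-sided is assumed.

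**The plan's own figure.**
- Standard error of a difference: 1.5 × √(2/200) = 0.15. Standardised difference: 0.5/0.15 = 3.33.
- Power: Φ(3.33 − 1.96) = Φ(1.37) = 91.5% (91.4% with the t distribution).
- n per group for 90%: 2 × (1.96 + 1.28)² × (1.5/0.5)² ≈ 190.

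So 200 per group is sufficient for that one comparison, and the arithmetic is correct.

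**Number of tests.** Four outcomes × three contrasts = 12. The third contrast compares two arms that see the same bar graph, so only 4 × 2 = 8 tests compare formats.

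**Chance of at least one false positive at 5% per test, no true differences.** If the tests were independent: 1 − 0.95¹² = 46.0% and 1 − 0.95⁸ = 33.7%. They are not independent, because the contrasts share the bar-graph-only arm and the outcomes are likely to be correlated. A simulation of 200,000 null trials per correlation, with 200 per arm and one score per outcome, gives:

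| Between-outcome correlation (assumed) | 0 | 0.3 | 0.5 | 0.7 |
|---|---|---|---|---|
| 8 format tests, no gate | 31.7% | 29.7% | 26.8% | 22.6% |
| 8 format tests, ANOVA gate per outcome | 11.9% | 11.3% | 10.4% | 8.8% |
| All 12 tests, no gate | 41.5% | 39.1% | 35.5% | 30.4% |
| All 12 tests, ANOVA gate per outcome | 15.1% | 14.3% | 13.1% | 11.3% |
| 8 format tests, no gate, higher score than bar graph only | 17.0% | 15.2% | 13.6% | 11.3% |

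For intention alone, the two format contrasts give 9.1% without a gate. All three contrasts give 12.5% without a gate and 4.0% with one.

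**Limit of the gate.** The gated figures assume that no arm differs. If the pre-questionnaire arm truly differs on an outcome, the four-group ANOVA tends to reject for that reason. The two format contrasts are then each read at 5%, and their joint error on that outcome approaches the ungated 9.1%.

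**Power per contrast at 200 per group (difference 0.5, SD 1.5), as Φ(3.33 − critical value).**
- Dunnett, two format contrasts: critical value 2.21, Φ(1.12) = 86.9%.
- Bonferroni, two format contrasts (alpha 0.025): 86.3%; 224 per group would restore 90%.
- Bonferroni, three contrasts on intention (alpha 0.0167): 82.6%; 244 per group.
- Bonferroni, 12 tests (alpha 0.00417): 68.0%; 310 per group, or 1,240 in all. This carries the 0.5 and 1.5 over to outcomes for which the document does not give them.

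**The case against.** The strongest reply is that this is a condensed article. Multiplicity adjustment and the role of the ANOVA are commonly left to an analysis plan, and the 5% level appears only in the sample size section, so reading every contrast at 5% is an assumption. That stands: the absence of an adjustment would not by itself be a finding. What remains is the contradiction over which outcome is primary. An unseen analysis plan could settle that only by overriding either section vii) or sections vi) and viii).

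A second reply is that the ANOVA may be meant as a gate. If so, the error for intention alone is about 4% when no arm differs. This also stands, and is why both readings are shown. Even then the error over four outcomes stays above 5%, and the gate fails when another arm truly differs.

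Two stronger readings are tempting but not supported. A reader might infer that a chance finding of an effective format is likely. Every scenario computed is below one half, the contrast between the two bar-graph arms cannot produce such a finding, and a false result in the higher-score direction has a chance of 17% to 11% even without a gate. A reader might also infer that worry cannot be an endpoint because its direction of benefit is unsettled: the Background says it may help or inhibit, and section viii) calls an increase possibly negative. But the stated objective asks which format induces most worry, and a two-sided comparison can answer that. The open direction limits interpretation and has no bearing on the error rate.

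**Conclusion.** The point holds as a contradiction within the document. Section vii) has one primary outcome and one comparison; sections vi) and viii) have four primary outcomes with three contrasts each and no order among them. Read at 5% per test with no true differences, the chance of at least one false format difference is about 32% to 23% ungated, or 12% to 9% gated. Over all 12 tests it is about 41% to 30%, or 15% to 11%. These figures assume two-sided tests, one score per outcome and a between-outcome correlation of 0 to 0.7, none of which the document gives. The stated 90% power is arithmetically sound but applies only to one unadjusted contrast on intention.

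**What to change.** Name intention as the single primary outcome in the abstract, Aims and Objectives, and sections vi) and viii), as section vii) already does. Make understanding, affect and worry secondary.

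Limit confirmatory testing to bar graph only v. pictogram and bar graph only v. metonym on intention. Use Dunnett or Holm, or an omnibus test of these three arms at 5% followed by pairwise tests at 5%, which is a closed procedure for three groups. If the four-group ANOVA is kept, say that it is descriptive and does not gate the contrasts.

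Restate power as about 87% per format contrast at 200 per group if Dunnett is used. Reconcile the status of the contrast between the two bar-graph arms in Aims and Objectives and section v), and keep it outside the confirmatory family.

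The cost is more than wording. Three outcomes now treated as primary lose that status, and the stated power falls by a few points. No extra recruitment is needed unless the sponsor wants a full 90% after adjustment; with Bonferroni for two contrasts that would be 224 per group, 896 in all. A stated hierarchy or an adjustment over all four outcomes would also resolve the contradiction, but would need a target difference and SD for each added outcome; a full Bonferroni adjustment would also lose more power.
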